#### Abbreviations:

AE – adverse event; BNP – brain natriuretic peptide; CBC – complete blood count; CRP – C-reactive protein; CT – Computed Tomography; CTA – CT angiography; DUS – Doppler ultrasound scan; ECG – Electrocardiogram; HADS – Hospital Depression and Anxiety Score; IS – Ischaemic Stroke; MoCA – Montreal Cognitive Assessment test; MRI – Magnetic Resonance Imaging; MRA – MRI angiography; mRS – modified Rankin Scale; NIHSS – NIH Stroke Scale; NOAC – non-vitamin K antagonist oral anticoagulant; NT-proBNP (N-terminal pro B-type natriuretic peptide); rtPA – recombinant tissue plasminogen activator;

#### Annotations:

a – AIS standard diagnostic (screening) procedures must follow national /local guidelines on stroke diagnosis and management; obtaining ICF; standard diagnostic procedures, allocation to the study group and randomisation should be completed **within 3.0 hrs of AIS onset**.

b – Study treatment includes sequential administration of NOAC specific antidote and thrombolytic treatment (rtPA) or corresponding placebo and administration of the thrombolytic component **should be initiated with 4.5 hr window (no later than 6h)** from AIS onset. The visit ends when all components of the study treatment are administered.

c – Visit 2 must occur at 24 hour (± 4 hours), visit 3 must occur on day 7 (± 1 day), visit 4 must occur on day 30 (± 2 days), visit 5 must occur on day 90 (± 3 day) after the start of administration of the thrombolytic component of study rtPA (or an appropriate placebo).

d – Study visits 0-3 are expected during hospitalisation (including stay in the emergency unit and neurology department); assessment visits 4 can be performed over the phone and 5 as an in person visit in the center (hospital).

e – Patients whose worsening neurological deficit makes it impossible to sign the consent form may give their oral consent to participate in the study. Patients with aphasia and/or other speech disorders may be included in the study if in the opinion of the qualifying physician are able to understand the idea of the study. For detailed information please refer to **the procedure of obtaining informed consent described in the Clinical Trial Protocol (Section 6.3)**.

f – After obtaining ICF patient will be allocated to one of the study group based on NOAC taken; group A – dabigatran; group B – apixaban, group C – rivaroxaban).

h – The first blood sample for determination of anti-IIa / anti-Xa activity or dabigatran blood concentration in the respective arm of the study (corresponding to NOAC plasma concentration) should be collected and processed immediately after obtaining ICF; patients with NOAC plasma concentration  $\leq 50$  ng/ml do not qualify for antidote administration and will be treated according to standard of care, which may include thrombolytic treatment. However, in patients on dabigatran, it is possible to enroll such a subject into the study based solely on a patient's or witness' report on the last intake of the anticoagulant ie, when it was administered within the last 24 hours preceding initiation of the study treatment. In these situations, it is obligatory to collect and store blood for post-hoc anti-IIa testing. The procedure is described in the Laboratory Manual.

i – The second blood sample for determination of anti-Xa (corresponding to NOAC plasma concentration) should be taken after NOAC-specific antidote bolus infusion (or corresponding placebo); the third blood sample should be collected after completion of rtPA (or corresponding placebo) administration.

j- Please note that in the STROACT trial we plan to estimate anti-IIa activity only in the pre-treatment stage of the study (a single measurement: either prospective ie, when treatment decisions are based on the blood test result, or retrospective ie, in cases where treatment decisions are based solely on drug administration history). Whereas anti-IIa 2nd (after infusion of NOAC-specific antidote bolus or corresponding placebo) and 3rd measurements (after completion of rtPA or corresponding placebo administration) are only facultative in this arm of the project. The second and third dabigatran blood measurements should not be performed.

k – Brain CT is preferred.

l – Mandatory examination for patients with **NIHSS  $\geq 6$**  or other clinical suspicion of Large Vessel Occlusion (LVO) and qualifying the patient to mechanical thrombectomy (exclusion from STROACT study).

m – Randomisation should be performed within 3.0 hrs from IS symptoms onset to allow timely preparation of the allocated study treatment to be initiated within 4.5 hr (not later than 6.0h) from the IS symptoms onset; **if randomisation time is  $>3.0$  hrs from the onset of IS symptoms investigator should consider patient withdrawal from the study.**

n – Preparation of the study treatment should be initiated immediately after receipt of the laboratory test results of anti-IIa or anti-Xa activity  $>50$  ng/mL or dabigatran concentration for the respective arm of the study. However, in patients on dabigatran, it is possible to enrol such a subject into the study based solely on a patient's or witness' report on the last intake of the anticoagulant ie, when it was administered within the last 24 hours preceding initiation of the study treatment. The procedure is described in the Laboratory Manual.

o – Infusion of the thrombolytic component of the study treatment (rtPA or corresponding placebo) should be initiated within 4.5 hr from the AIS onset, but **no later than within 6 hours from AIS onset**, otherwise participant should be withdrawn from the study.

p – In case of initiating thromboembolic prophylaxis, i.e., starting antiplatelet agents, heparins or OAC/NOAC, the information about type of medication, dosage and time of initiating treatment should be entered in patient's medical records and on eCRF (see [Section 7.6.1](#))

q – In women of childbearing potential urine pregnancy test must be performed or a blood pregnancy test if urine cannot be obtained. Females of childbearing potential and women in a postmenopausal state: females of childbearing potential and women with no menses for a period < 12 months must have a negative pregnancy test at Visit 0 and have to agree not to start a pregnancy from the signature of the informed consent up to the Final Visit, using an appropriate birth control method such as combined oestrogen-progestin containing hormonal contraceptives (e.g., oral, injectable, transdermal), progestin-only hormonal contraceptives (e.g., oral, injectable, implantable), intrauterine device (IUD) or intrauterine hormone-releasing system (IUS) in combination with male condom, bilateral tubal occlusion, vasectomised partner, sexual abstinence.

**Woman of childbearing potential (WOCBP):** i.e., fertile, following menarche and until becoming post-menopausal, unless permanently sterile. Permanent sterilization methods include hysterectomy, bilateral salpingectomy and bilateral oophorectomy.

**Postmenopausal state** is defined as no menses for 12 months without an alternative medical cause.

r – Assessments in brackets are optional (to allow data collection if available), and if they interfere with standard diagnostic assessments, they are not clinically justified, or may significantly delay initiation of investigational treatment may not be performed; missing data for these assessments will be not considered as protocol deviations.

s - The test should be performed at least once during hospitalization (V0-V3)

t - Obligatory only in cases where the screening value was beyond that defined in inclusion/exclusion criteria.

u - ECG must be performed preferably within the first 24 hours from AIS but not later than 72 hours.

w- Review of safety endpoints: any symptomatic intracranial haemorrhage (sICH), any life threatening extracranial bleeding, recurrent or new acute thromboembolic stroke, any life threatening thromboembolic complications, any significant allergic reactions assumed to be related with the administered substances (antidotes, rtPA).

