### 2.3.1 KNOWN POTENTIAL RISKS

Patients with AIS are the population with multiple and various comorbidities, and high total cardiovascular risk.

The most severe complication related to rtPA administration is symptomatic intracerebral haemorrhage (sICH), which occurs in 3-7% of all treated patients, and is associated with poor functional outcome (Hacke W et al, 2008) (Sandercock P et al, 2012) (Karaszewski B et al, 2015) (Yaghi S et al., 2014). Meta-analysis of nine trials of rtPA in ischemic stroke (Whiteley WN et al, 2016) showed increased risk of type 2 parenchymal haemorrhage (PH2), of haemorrhage as per SITS-MOST definition, and fatal intracerebral haemorrhage in IVT group.

In REVERSE-AD trial (A Study of the RE-VERSAl Effects of Idarucizumab on Active Dabigatran), a multicentre, prospective, open-label study, patients with life-threatening or uncontrolled bleeding and patients who required emergency surgery or other urgent procedures, were treated with 5.0 g of intravenous idarucizumab. Median maximum reversal value was 100% in the first 4 hrs. Most patients achieved complete reversal as measured by ECT (82%), or dTT (99%). The adverse reactions reported in ≥5% of patients were constipation and nausea. In 33 (6.56%) patients reported thrombotic

events, and most of these patients were not on antithrombotic therapy at the time of the event (Pollack CV et al, 2017).

In ANNEXA-4 trial (The Andexanet Alfa, a Novel Antidote to the Anticoagulation Effects of Factor Xa Inhibitors), a single-group cohort study, patients with acute major bleeding – 64% intracranial and 26% gastrointestinal – were treated with andexanet alfa in intravenous bolus over 30 minutes, followed by continuous infusion for 120 min. Median anti-FXa activity decreased was 92% for both apixaban and rivaroxaban patients. There were 34 patients (10%) with a thrombotic event during 30-day follow-up period (Connolly SJ et al, 2019).

---

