Eligible patients allocated to each study group will be randomised at 1:1 ratio to receive experimental treatment or corresponding placebo (see section 6.4). Study treatment is composed of sequential intravenous administration of NOAC-specific antidote (or placebo) followed by the infusion of rtPA or corresponding placebo.

Standard diagnostic procedures, allocation to the study group and randomisation should be completed within 3.0 hrs from AIS symptoms onset to minimise the risk of delay to start of the study treatment. Randomisation scheme will include severity of the IS at randomisation (<6 points, and  $\geq 6$  points in NIHSS) as a stratification factor in all 3 study groups (arms).

Administration of rtPA should be initiated within 4.5h time window calculated from the onset of AIS symptoms but no later than 6h in specific circumstances (correctly performed randomisation process and administration of the antidote, unavoidable factors delaying administration of rtPA beyond 4.5 hours).

After receiving study treatment patients will be assessed at 24 (+/-4) hrs (Visit 2), 7 (+/-1) days (Visit 3), 30 (+/-2) days (Visit 4), and 90 (+/-3) days after rtPA bolus treatment administration and collected data will be recorded in the eCRF (please see Schedule of Assessments [SoA] in [Section 1.3](#))

An Independent Data Monitoring Committee (IDMC) will be established before the start patients' enrolment to monitor progress of the clinical study and to ensure participants' safety. This will include reviewing unblinded safety and the efficacy data, estimating the benefit-risk balance during the study and supervising the overall conduct of the study.

The composition and responsibilities of the IDMC will be described in the IDMC charter.

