### 5.1 INCLUSION CRITERIA

To be eligible for enrolment patient **must meet all** the following inclusion criteria:

1. Obtaining informed consent to participate in the trial prior to randomisation.

**NOTE:** Patients whose neurological deficit is severe enough to make it impossible to sign the consent form are allowed to give only their oral consent to participate in the study. However, this consent should be additionally certified by the signature of two independent witnesses (who are neither family members of the patient nor the STROACT study staff) or by the signature of his/her legal representative. **Patients with aphasia and/or other speech disorders may be included into the study if following neurological assessment of the recruiting stroke physician, they are able to understand all important information about the study.**

2. Age  $\geq 18$  years.
3. Clinical diagnosis of acute ischemic stroke (sharply defined onset of first symptoms) resulting in a disabling neurological deficit.
4. Therapy with an oral anticoagulant that is the non-vitamin K antagonist oral anticoagulant (dabigatran, apixaban, or rivaroxaban) with laboratory confirmed therapeutic anti-IIa/anti-Xa activity measured as a plasma concentration  $> 50$  ng/mL or the corresponding blood concentration of dabigatran (in the respective arm of the study). However, in patients on dabigatran, it is possible to enrol such a subject into the study based solely on a patient's or witness' report on the last intake of the anticoagulant ie, when it was administered within the last 24 hours preceding initiation of the study treatment. In these cases it is obligatory to collect and store blood for post-hoc anti-IIa testing.
5. Administration of study intervention (intravenous thrombolysis with alteplase or placebo) should be possible to start within 4.5 hours from AIS symptoms onset or the last time the patient was seen without symptoms, as per investigator's judgment.

**NOTE:** If patient had been randomised and there was an explicit clinical justification for delay in starting study intervention within 4.5h window, patient might continue in the study if rtPA (or rtPA placebo) could be administered within 6.0h from AIS onset.

**NOTE:** In patients recruited to STROACT study, in addition to the inclusion / exclusion criteria, apply all standard clinical practice indications and contraindications for rtPA administration in acute ischemic stroke unless stated otherwise in this protocol.

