## 8 STUDY INTERVENTION DISCONTINUATION AND PARTICIPANT DISCONTINUATION/WITHDRAWAL

### 8.1 DISCONTINUATION / INTERRUPTION OF STUDY INTERVENTION

It may be necessary for a participant to permanently discontinue study intervention. If study intervention is permanently discontinued, the participant will remain in the study to be evaluated for efficacy and safety parameters as appropriate.

Study treatment may be permanently discontinued because of:

- Informed decision of the patient
- The investigator's decision resulting from:
  - Finding of incorrect randomisation of the patient, due to which there is a risk to the health or life of the patient (non-compliance with the criteria for inclusion / exclusion of the patient in the study).
  - Adverse reactions that the investigator believes may lead to a deterioration in the patient's health (irrespective whether related or not to the treatment used).

Temporary suspension of study treatment administration should occur if during the second phase of treatment (rtPA or placebo) if systolic blood pressure rises above 185 mmHg and/or diastolic blood pressure above 110 mmHg.

If the blood pressure cannot be lowered below 185/110 mmHg within 15 minutes, then the study treatment should be permanently discontinued.

NOTE: Premature termination of the study treatment for any reason does not mean termination of the patient's participation in the study - the patient should be further evaluated according to the study protocol (at day 2, 7, 30 and 90).

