### 11.4.3 SAFETY ANALYSIS POPULATION (SAF)

A subset of intent to treat analysis population consisting of subjects that received study treatment. This population will be used for all safety analyses.

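### The rule for a patient whose rtPA or placebo is not started by 6 h contradicts Sections 8.1 and 8.2: one withdraws the patient from the study, the others keep the patient in follow-up

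*Protocol*

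**What the plan says.** Annotation o in Section 1.3 asks for the thrombolytic component to be started within 4.5 h of onset and at the latest within 6 h, "otherwise participant should be withdrawn from the study". The note to inclusion criterion 5 (Sections 1.1.5.1 and 5.1) points the same way: after a justified delay, the "patient might continue in the study if rtPA (or rtPA placebo) could be administered within 6.0h from AIS onset".

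Section 8.1 states the opposite consequence: "If study intervention is permanently discontinued, the participant will remain in the study to be evaluated for efficacy and safety parameters as appropriate". Its closing note extends this to premature termination for any reason and adds that "the patient should be further evaluated according to the study protocol (at day 2, 7, 30 and 90"). Section 8.2 agrees that stopping the acute therapy is not automatic exit from the study.

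Sections 4.1 and 6.4.4 bar rtPA after 6 h but do not order study withdrawal. Section 4.1 describes the setting in which rtPA may be given after 4.5 h: "correctly performed randomisation process and administration of the antidote, unavoidable factors delaying administration of rtPA beyond 4.5 hours".

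Annotation c times Visits 2 to 5 "after the start of administration of the thrombolytic component of study rtPA (or an appropriate placebo").

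**The concern.** The antidote comes first in the sequence, so a patient can have received it, or its placebo, before the 6 h limit passes. For that patient study treatment has begun and is then not completed. Annotation o removes the patient from the study and Section 8.1 keeps the patient in it. Two sites reading different pages would handle identical patients differently.

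Two things are at stake. The first is safety information. In the active group these patients have had their anticoagulation reversed without thrombolysis, and Section 7.6.1 itself warns that reversal leaves patients open to the thrombotic risk of their underlying disease. Section 2.3.1 reports for andexanet in another population, patients with acute major bleeding: "There were 34 patients (10%) with a thrombotic event during 30-day follow-up period". The second is completeness of the randomised comparison. Section 11.4.1 places every randomised patient in ITT, so a protocol-ordered withdrawal creates missing day 90 mRS values after randomisation that could have been avoided. The same patients also drop out of the per-protocol set, which Section 11.4.2 defines by having that assessment.

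**Working it through.** **Passages side by side**

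| Question | Annotation o and criterion 5 note | Sections 8.1 and 8.2 |
|---|---|---|
| rtPA/placebo not started by 6 h: what happens? | Withdrawn from the study; continuing depends on rtPA/placebo within 6 h | Treatment ends, participation does not |
| Exception if the antidote was given? | None | None needed; 8.1 covers any reason |
| Follow-up | None scheduled | Days 2, 7, 30 and 90 |

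**What is lost under annotation o.** The 24 h and day 7 imaging, day 7 and 90 NIHSS, day 7, 30 and 90 mRS, and visit-based recording of deaths and events. Section 11.1.3 uses data only up to withdrawal.

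**What is kept.** Section 9.3.1 requires events ongoing at treatment discontinuation, and new treatment-related events within 30 days, to be followed to resolution or stability. Sections 9.3.2 and 9.3.3 collect AEs to end of study and require all SAEs to be reported. None of these replaces scheduled imaging or mRS, or events not judged treatment-related.

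**What following 8.1 leaves open.** Annotation c anchors every later visit on the start of rtPA or placebo. A patient kept in the study without it has no start point for the visit windows in that annotation.

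**Effect on sample size and power.** Inputs from Section 11.3: 40% response in both groups, margin 15 percentage points, one-sided level 0.2, power 70%, drop-out 10%, one interim.

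1. Fixed design: n = 2 × 0.4 × 0.6 × (0.8416 + 0.5244)² / 0.15² = 0.48 × 1.866 / 0.0225 = 39.8 per group.
2. One interim at half information with Hwang-Shih-DeCani spending. The parameter is not stated. Taking −4 gives an interim level of 0.2 × (1 − e²)/(1 − e⁴) = 0.0238, which matches Section 11.5.4.1. The size becomes 40.05, rounded up to 41, and 41/0.9 = 45.6, so 46. The plan's figure of 46 per group is reproduced.
3. The protocol gives no rate for patients caught by annotation o. Assume a share w on top of the 10% drop-out, so that evaluable patients per group = 46 × (0.90 − w):

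| w (assumed) | Patients per group, 46w | Over three active groups, 3 × 46w | Evaluable per group | Power |
|---|---|---|---|---|
| 0 | 0 | 0 | 41.4 | 70.8% |
| 2% | 0.9 | 2.8 | 40.5 | 70.3% |
| 5% | 2.3 | 6.9 | 39.1 | 69.4% |
| 10% | 4.6 | 13.8 | 36.8 | 68.0% |

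Power uses the final boundary that follows from the spending function (nominal level 0.197). With the plan's stated final level of 0.176 the loss at w = 5% is the same: 68.1% falls to 66.7%, or 1.4 points.

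**The case against.** The best defence is that Section 8.1 is the section dedicated to discontinuation, that it speaks of any reason, and that a Schedule footnote should give way to it. On that reading nobody is lost. This is a sensible way to resolve the conflict, but the protocol does not say so, and the criterion 5 note sides with the footnote. It stands to this extent: follow-up is lost only where a site follows annotation o.

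The case is also narrow. Annotation o does not mention the antidote, and Section 4.1 describes a delay beyond 4.5 h, not beyond 6 h. Randomisation is aimed at 3 h. The andexanet bolus takes about 14 or 27 minutes, with rtPA starting alongside or directly after the infusion begins. Antidote given and rtPA not started by 6 h should be uncommon. That limits the size but does not remove the contradiction.

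Four stronger readings are tempting and are not supported:

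- A reader might infer that deaths and thrombotic events in these patients go wholly uncounted. Sections 9.3.1 to 9.3.3 preserve part of them.
- A reader might infer that the safety population excludes them, because it requires patients to have received study treatment ("A subset of intent to treat analysis population consisting of subjects that received study treatment") and the notes to Figure 2 define that treatment as antidote and rtPA together. Section 6.4.4 calls rtPA the second component, and Section 11.5.2.6 counts treatment-emergent events from the first administration of study medication, so inclusion is at least as natural a reading. Detailed population rules are left to the SAP.
- A reader might infer that loss must be unequal because delays arise only with active drug. Neurological deterioration can delay rtPA placebo too, and annotation o applies to both groups. Unequal loss is possible, since only active patients can react to the antidote, but it is not shown.
- A reader might set one missed event among 46 patients against the quoted 3–7% rate of symptomatic haemorrhage. That rate is a different outcome in patients who did receive rtPA, so the comparison carries no information here.

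**Conclusion.** Annotation o and the criterion 5 note contradict Sections 8.1 and 8.2 on whether a randomised patient without rtPA or placebo by 6 h stays in the study. The passages must be reconciled. The conflict is clearest for a patient already given the antidote or its placebo, because treatment has then begun.

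The consequence is conditional on a site following annotation o. It is then the loss of scheduled imaging and day 7, 30 and 90 outcomes, not of all safety information. The number affected is unknown and probably small: about 1 to 2 per randomised group if 2% to 5% are affected, which is an assumption with no basis in the protocol. The effect on power is negligible. The point rests on safety follow-up and ITT completeness in a treatment sequence that Section 2.3 calls the first ever studied. No view is taken on the 6 h limit.

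**What to change.** 1. **Annotation o and the criterion 5 note.** Reconcile them with Sections 8.1 and 8.2 so that not starting rtPA or placebo is kept separate from leaving the study. Randomised patients would then be followed to Day 90 unless consent is withdrawn. The time limit for rtPA stays with the clinical leads.
2. **Annotation c.** Add a fallback visit anchor for patients in whom rtPA or placebo is not started, for example the start of the antidote or its placebo.
3. **Section 11.4.3 (helpful clarification, not correction of a demonstrated error).** State that the safety population includes anyone in whom any component of study treatment was started.

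The cost is a few wording changes in one amendment, plus the routine scheduled visits for what is probably a handful of patients, who are already in hospital when the limit passes. The sample size does not change.
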